## Abstract

**Background:**

Sexual and gender minorities (SGM) experience among the largest mental health disparities of any population. One driver has been the lack of evidence-based practices (EBPs) addressing the distinct mechanisms underlying SGM’s risk. LGBTQ-affirmative cognitive-behavioral therapy (CBT) is among the only EBPs specifically for SGM mental health. LGBTQ community centers represent an ideal implementation setting for LGBTQ-affirmative CBT given their wide reach. Although direct training of mental health providers at LGBTQ community centers by experts has been shown to improve providers’ LGBTQ-affirmative CBT skills, it is unclear how such training should be optimally delivered. This paper describes the protocol of a trial that seeks to compare the effectiveness of three training strategies for implementing LGBTQ-affirmative CBT, identify center-level moderators of implementation success, and examine the impact of the three strategies on client mental health through theory-informed organizational and provider mechanisms.

**Methods:**

This hybrid type III effectiveness-implementation trial will randomize 90 centers to receive one of three additive strategies for implementing LGBTQ-affirmative CBT: [1] a suite of self-paced digital learning materials (Materials Only condition); [2] these materials plus weekly live webinar training for 12 weeks (Direct Training condition); or [3] the above plus one year of supervision from a local supervisor who will receive expert consultation in a train-the-trainer format (Local Supervision condition). The primary outcome will be provider fidelity assessed via simulated practice. Implementation determinants (e.g., center resources, provider/client characteristics), mediators (e.g., implementation climate, provider self-efficacy), and other outcomes (e.g., intervention adaptation, sustainment) will be captured using a mixed-methods design. Clinical effectiveness outcomes (i.e., client mental and behavioral health symptoms) will be assessed through client surveys among a subset of 15 centers.

**Discussion:**

Now that LGBTQ-affirmative CBT has shown efficacy across several trials and generated high demand, research is needed to determine nationwide implementation strategies. This study will identify optimal means through which to implement this treatment innovation in the US’s large network of LGBTQ community centers, thereby producing generalizable guidance for EBP implementation across low-resource settings nationwide in which mental health disparities populations are likely to seek treatment.

**Trial registration:**

NCT05890404 (05/25/2023), https://clinicaltrials.gov/study/NCT05890404.

**Supplementary Information:**

The online version contains supplementary material available at 10.1186/s12913-025-13136-3.

## Background

Sexual and gender minority (SGM) individuals experience a significantly elevated risk of adverse mental health conditions; specifically, consistent evidence suggests that SGM individuals are at a 1.5-4 times greater risk for depression, anxiety, substance use problems, and suicidality compared to the general population [1–6]. These disparities are driven by LGBTQ-related stigma [2, 7] from the broadest structures (e.g., laws and policies denying, or failing to protect, SGM equality [8]) to daily events (e.g., bullying, family rejection [9–11]). This stigma gives rise to LGBTQ-related stress reactions, at least partially explaining SGM individuals’ elevated risk of poor mental health [12–16]. These stress reactions include cognitive (e.g., hypervigilance), affective (e.g., shame), and behavioral (e.g., concealment) processes [17, 18]. Bisexual, transgender, and racial/ethnic minority SGM are at particular risk for mental health challenges due to intersectional forms of stigma [19–22].

SGM individuals experience several barriers to accessing affirmative mental health care that is responsive to stigma-related stress reactions, thereby perpetuating the disparity [23–26]. For instance, SGM individuals report shame in discussing their stigma experiences and often mistrust mental health providers, perhaps because of the historical anti-SGM stance of the mental health field, the continued practice of harmful so-called “conversion therapies,” and mental health providers’ role as gatekeepers of some forms of care [27–33]. The lack of evidence-based practices (EBPs) — practices supported by research evidence — that affirmatively address SGM individuals’ distinct stigma-related concerns have also historically impeded SGM people’s treatment access, further perpetuated by a lack of available mental health providers trained in affirmative treatment approaches [31, 34].

LGBTQ-affirmative cognitive-behavioral therapy (CBT) was developed to bring scientific evidence and stigma theory to bear on SGM people’s mental health care [35, 36]. It is one of the first mental health treatments with efficacy drawn from clinical trials showing evidence for improving SGM mental health [37, 38]. LGBTQ-affirmative CBT contains nine modules that focus on minority stress awareness, strategies for challenging internalized stigma, emotion awareness and regulation, and behavioral skills to mitigate minority stress reactions [39, 40]. The treatment encourages providers to create a case conceptualization that considers the early and ongoing role of minority stress in each client’s current distress [41]. Typically administered individually by a trained mental health provider, the treatment can be delivered in as few as ten sessions or extended based on clinician judgement. LGBTQ-affirmative CBT is particularly suited to addressing SGM’s mental health given that it identifies social determinants of mental health (rather than internal deficits), facilitates insight into internalized stigma (rather than questioning the existence of stigma), and promotes coping self-efficacy [42]. LGBTQ-affirmative CBT also lends itself to implementation in frontline settings given that it is skills based, present focused, and time limited [43–47].

The efficacy of LGBTQ-affirmative CBT has been tested across several randomized controlled trials with various SGM populations. In two early waitlist trials (*n* = 63 young sexual minority men; *n* = 60 young gender-diverse sexual minority women), LGBTQ-affirmative CBT yielded moderate-to-large reductions in depression, anxiety, and alcohol use [37, 38]. These trials also found significant engagement of the hypothesized target mechanisms: internalized homonegativity, social isolation, and emotion dysregulation. In a larger trial (*n* = 254 sexual minority men), LGBTQ-affirmative CBT was particularly efficacious in reducing substance use problems and mental health comorbidity compared to two control conditions– treatment-as-usual and screening/brief intervention/referral [48]. Moderator analyses showed that LGBTQ-affirmative CBT was most efficacious in addressing comorbid depression, anxiety, substance use problems, and HIV-transmission-risk behavior among Black and Latinx men [49]. Additional trials have found support for LGBTQ-affirmative CBT’s initial effectiveness and strong acceptability among Black and Latinx sexual minority men [50], sexual minority young men in China [51], and transgender and gender-nonbinary individuals [52].

Few nationwide settings exist for studying the implementation of mental health innovations like LGBTQ-affirmative CBT. However, the US has over 300 LGBTQ community centers that meet the SGM community’s otherwise-unaddressed social, legal, and health needs. LGBTQ community centers are those with a primary goal to support the LGBTQ community by offering formal programming, from support groups to comprehensive health care [53, 54]. Given their role in serving over 48,000 clients/year, most of whom are Black and Latinx and earn <$30,000/year [55], LGBTQ community centers represent a promising venue in which to address the disproportionate mental health challenges affecting SGM individuals by training providers to deliver LGBTQ-affirmative CBT. Our team prepared for the implementation of this treatment in LGBTQ community centers through stakeholder meetings [56], center director surveys [56], a pilot training study [57], and interviews with implementers [58]. Through this work, we learned that training providers at LGBTQ community centers in LGBTQ-affirmative CBT is feasible, acceptable, and efficacious. Center directors strongly endorsed the need for their mental health providers to be trained in LGBTQ-affirmative CBT and unanimously supported allowing staff time for this [56].

In a waitlist trial across 50 centers, mental health providers (*n* = 120) rated a 12-week (one hour per week) training in LGBTQ-affirmative CBT to be informative and motivating, and results showed that the training improved their competence, knowledge, and skills in LGBTQ-affirmative CBT [57]. Other data show that mental health providers in clinical trials of LGBTQ-affirmative CBT have rated ongoing supervision as the most effective implementation support [58]. Although EBP training and supervision is generally effective, recent systematic reviews identify three knowledge gaps for the field of EBP training overall [59–61], including: (1) whether train-the-trainer strategies can sustain EBP implementation beyond any initial training; (2) whether features of resource-constrained settings, characterizing many LGBTQ community centers (e.g., high staff turnover), predict the optimal EBP implementation strategy needed; and (3) the target mechanisms through which EBP training impacts implementation *and* client outcomes.

To date, LGBTQ-affirmative CBT has only been tested in controlled trials in research settings [37, 38, 48, 49, 62, 63]. At the same time, mental health providers working in real-world settings (e.g., Veterans Health Administration, college counseling centers, community mental health) have begun implementing the treatment without evaluation since the publication of the treatment manuals [39, 40]. While this reflects the high demand for this treatment, it has not produced generalizable knowledge about implementation. In this current trial, we draw on two implementation frameworks, Reach, Effectiveness, Adoption, Implementation, and Maintenance (RE-AIM) [64] and the Consolidated Framework for Implementation Research (CFIR) [65, 66], to conduct a type III hybrid effectiveness-implementation trial to test LGBTQ-affirmative CBT’s real-world effectiveness and implementation outcomes across three additive training conditions — i.e., the three implementation strategies tested in this trial: (1) a self-paced suite of digital learning materials, including provider guides and training videos (Materials Only condition); (2) these material plus a weekly live webinar training for 12 weeks (Direct Training condition), or (3) the above plus supervision from a local supervisor who themselves will receive expert consultation in a train-the-trainer format (Local Supervision condition).

We hypothesize that these three additive training implementation strategies will predict respective graduated increases in implementation success at 4-, 8-, 12-, and 24-months post-training (see Figs. 1 and [67]). That is, we predict that reach, effectiveness, adoption, implementation, and maintenance will be higher in the Local Supervision condition relative to the Direct Training condition and that the Direct Training condition’s implementation outcomes will be higher than the Materials Only condition. Drawing on theories of organizational [68, 69] and provider [70–73] change, we also hypothesize that organizational (e.g., shared norms of the importance of EBP) and provider (e.g., self-efficacy for EBP delivery) factors will mediate the stronger impact of the more intensive training strategies on implementation success and client mental health outcomes. To facilitate this latter aim, in a subset of 15 LGBTQ community centers (five centers per condition), we will compare the three training implementation strategies in terms of client mental health symptom change from before implementation to 4, 8, 12, and 24 months after.

**Fig. 1 Fig1:**
[figure not shown]
Implementation research logic model for comparing three training strategies to enhance the implementation of LGBTQ-affirmative CBT in LGBTQ community centers

## Methods

### Aims

This trial employs a type III hybrid effectiveness-implementation design to pursue the following three aims:

Compare the success of three additive LGBTQ-affirmative CBT implementation strategies (Materials Only, Direct Training, and Local Supervision) across 90 LGBTQ community centers.Identify center-level determinants of successful implementation of LGBTQ-affirmative CBT.Examine the impact of three implementation strategies on client mental health through theory-informed target mechanisms at both organizational and provider levels.

### Setting

We will implement one of these three LGBTQ-affirmative CBT training strategies at 90 LGBTQ community centers in the US. Of the more than 300 LGBTQ community centers in the US, about 200 provide mental health services [55, 56]. The 90 centers will be selected based on responsiveness and capacity (e.g., anticipating at least two providers who would participate in the training). The 90 included centers for this study will represent every region of the US, serve urban and rural areas, and represent the majority of US states. With small operating budgets, these centers are often staffed by mental health trainees and peer volunteers [55]. Further, most centers currently offer non-EBP supportive therapy [56]. Enhancing LGBTQ community centers’ capacity to implement LGBTQ-affirmative CBT would (1) bring EBP to thousands of SGM clients per year, (2) train early-career mental health providers to bring this EBP to their future work settings, and (3) identify the best strategies and organizational and provider targets for implementing EBPs for disparity populations in low-resource settings nationwide.

### Design

A type III hybrid effectiveness-implementation design has been selected given that efficacy for this treatment has already been established while real-world effectiveness has not [37, 38, 48, 51, 74, 75]. LGBTQ community centers will be randomly allocated to one of the three implementation strategies for the duration of the study. Because randomization will occur at the center level, mental health providers working in the same center will receive the same one of the three training strategies, each described in further detail below. This cluster-randomized design has been selected to imitate the real-world context of EBP implementation (that is, change in provider practice typically occurs at the organization-level) [76], promote equity across providers working at the same center, and accommodate EBP diffusion across providers working at the same center.

To assess implementation outcomes, determinants, and mechanisms, we will collect survey data from mental health providers (*n* = 540), local supervisors (*n* = 30), and directors (*n* = 90) at baseline and 4-, 8-, 12-, and 24-month follow-ups. Interview data will be collected from providers, directors, and local supervisors throughout the follow-up period selected according to a sampling matrix designed to ensure equal distribution across geographic regions, center budget, and implementation condition among interviewees. The study flow for Aims 1 and 2 is illustrated in Fig. 2. To assess effectiveness outcomes (Aim 3), a subset of 15 centers have agreed to administer brief surveys with standardized symptom checklists and demographic questionnaires to their clients (*n* = 780) over the course of the study (see Fig. 3). Mental health providers, directors, local supervisors, and clients will be compensated for each survey and interview completed, and continuing education credits will be offered for each training module completed.

**Fig. 2 Fig2:**
[figure not shown]
CONSORT: Study flow for mental health provider and director participants

**Fig. 3 Fig3:**
[figure not shown]
CONSORT: Study flow for client participants

### Center enrollment

We have partnered with CenterLink, an international nonprofit organization and network of LGBTQ community centers. At least 200 CenterLink-affiliated centers provide mental health services, and others offer referrals to local mental health providers [55]. We will send targeted email communications to directors of these centers, informing them of this trial and training opportunity. Centers are eligible to enroll in this trial if they are (1) a current member of the CenterLink network, (2) based in the United States, and (3) anticipate at least two providers associated with their center participating in the training/study. Directors at centers that meet these criteria will sign a memorandum of understanding to officially enroll their center into the trial. We aim to enroll 90 centers.

In addition, 15 of the 90 enrolled centers will be selected to participate in Aim 3 of the study, in which they will additionally be asked to facilitate the collection of client mental health data at baseline and through the 24-month follow-up through activities such as distributing information about the survey to their mental health clients. These 15 centers were selected a priori to represent diversity across geographic region, budget, and populations served. Shortly before client data collection begins, these centers will be mailed palm cards containing client recruitment text alongside instructions regarding how to introduce the survey to clients.

### Randomization

Upon receiving 90 signed memoranda of understanding, the 90 LGBTQ community centers will be randomized in a 1:1:1 ratio to receive one of the three implementation strategies. Randomization will be stratified by director report of anticipated staff participation. Specifically, high-attendance centers will be operationalized as those with greater than the median number of anticipated providers across the 90 enrolled centers whereas low-attendance centers will be operationalized as those that anticipate fewer than the median number of providers per center. Centers whose anticipated number of providers is at the median will be randomly and evenly divided across the two groups. The 15 effectiveness centers will be randomized separately to ensure their equal distribution across the three implementation strategies. Randomization allocation will be generated by the study statistician and assigned by the study coordinator. All participants and study staff will be unmasked to condition assignment, as necessitated by the study design.

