#### Provider implementation fidelity outcome analyses

We will summarize provider characteristics (e.g., volunteer status, length of SGM service) overall and by implementation strategy and assess for baseline imbalances. We will then compare the implementation outcomes for the Materials Only condition vs. Direct Training vs. Local Supervision. The primary implementation outcome is provider implementation fidelity (assessed via simulated practice responses) at 8-month follow-up; secondary outcomes include 8-month provider self-efficacy, competency, familiarity, and use of LGBTQ-affirmative CBT. For primary and secondary outcomes, will use mixed effects models [93] with the identity link function to compare the effect of implementation strategies. The fixed effects include the time effect and the time × implementation strategies interaction terms; the random effects include center and within-provider repeated measures. We will use the robust score test to assess whether the interaction terms are significantly different across the three strategies, with a 0.05 overall Type I error rate, and a 0.025 error rate for each of the two primary strategy comparisons. For secondary outcomes, we will compare implementation strategies with a 0.05 Type I error rate. We will re-run these analyses with 12- and 24-month outcomes to determine implementation maintenance.

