##### Sample size justification

Provider implementation fidelity serves as our primary outcome used to estimate sample size given its role in linking provider behavior to client mental health [84, 94–96]. We estimate that approximately six mental health providers will enroll per center, or about 540 providers total. Power was computed to test the null hypotheses of no difference between Materials Only and Direct Training and between Direct Training and Local Supervision in a cluster trial. For the primary implementation outcome, the change from baseline to 8-month follow-up was estimated as 0.14 for the Direct Training strategy and its variance was estimated as 0.0439 using data obtained from the waitlist-controlled trial [57]. Thus, the standardized change for the Direct Training strategy was estimated at 0.67. With a 0.025 Type I error rate, allowing for two primary comparisons between the three strategies, we will have 80% power to detect an effect of *d* = 0.34–0.46 on the 8-month change of the primary outcome, assuming a between-center ICC ≤ 0.1. In other words, we will have 80% power to detect the difference between Materials Only and Direct Training when the standardized change for Materials Only is ≤ 0.21–0.33, and we will have 80% power to detect the difference between Direct Training and Local Supervision when the standardized change for the Local Supervision strategy is ≥ 1.01–1.13.

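### The stated Aim 1 fidelity model has no term for the factors used to randomize centers; if these predict change in fidelity, the primary test is conservative and loses a little power

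*Protocol article*

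**What the plan says.** Under Randomization, the protocol article allocates 90 centers 1:1:1 to the three strategies and restricts that allocation in two ways. First, "Randomization will be stratified by director report of anticipated staff participation": centers are classed as high or low attendance by a median split, and centers at the median are divided at random between the two groups. Second, "The 15 effectiveness centers will be randomized separately to ensure their equal distribution across the three implementation strategies".

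Under Provider implementation fidelity outcome analyses, the primary model is written out. On the fixed part: "The fixed effects include the time effect and the time × implementation strategies interaction terms". On the random part: "the random effects include center and within-provider repeated measures". The test is a robust score test of the interaction terms, with "a 0.025 error rate for each of the two primary strategy comparisons". Neither the participation stratum nor effectiveness-center status appears.

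The only outcome comparison for which covariate adjustment is named is the client analysis (Effectiveness outcome analysis). There, client factors and center-level covariates such as rurality and size enter sensitivity analyses. That does not reach the Aim 1 fidelity outcome.

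**The concern.** Stratified allocation makes the arms alike on the stratifying factor, so that factor contributes almost nothing to the real sampling variation of the difference between arms. A model without the factor does not know this. It leaves the factor's variance in the center-level variance and reports a standard error that is too large. A robust variance does not repair this, because it treats centers as independently allocated and takes no account of the balance that was imposed.

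The tested quantity is time by strategy, so what matters is whether the factors predict *change* in fidelity. Anticipated participation reflects center size and engagement, which may bear on how much providers gain. The effectiveness centers were picked in advance for diversity of region, budget and population served (Center enrollment) and also take on client data collection, so they may differ from the other 75. If either factor is prognostic, the two primary comparisons run below their stated 0.025 and lose some power with 30 centers per arm.

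**Working it through.** **Inputs from the protocol article.** 90 centers, 1:1:1, so 30 per arm (Randomization); about six providers per center, 540 in total; between-center ICC at most 0.1; change 0.14 with variance 0.0439; 80% power for d = 0.34–0.46 (all from Sample size justification for the provider outcome); alpha 0.025 per comparison. Sidedness is not stated; two-sided is assumed, so z = 2.241, and z for 80% power is 0.842.

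**The plan's own figures first.** Standardized change: 0.14/√0.0439 = 0.668, matching the stated 0.67. Detectable effect without loss: d = (2.241 + 0.842) × √(2 × [1 + 5 × ICC]/180). This gives 0.325 at ICC 0 and 0.398 at ICC 0.1. A t reference gives about 0.33–0.41. The stated lower end of 0.34 is reached at ICC 0.01 with a t reference. The upper end of 0.46 needs something the section does not state, such as about 30% provider loss at ICC 0.1 (0.456) or strongly unequal center sizes. The stated range is plausible and is not disputed here.

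**Effect of the omission.** Let R² be the share of between-center variance in change explained by the randomization factors. The documents give no value; 0–0.3 is an assumption.

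- Center share of the variance of a center mean: c = ICC/(ICC + (1 − ICC)/6)
- Share of the modeled variance that is not real sampling variation: s = c × R²
- Actual size of the unadjusted test: 2[1 − Φ(2.241/√(1 − s))]
- Gain from adjusting, as extra centers: 1/(1 − s) − 1
- At the effect for which the unadjusted calculation gives 80%, power without the terms is Φ(0.842/√(1 − s)), and with them Φ(3.083/√(1 − s) − 2.241)

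Worked at ICC 0.1, R² 0.3: c = 0.10/(0.10 + 0.15) = 0.40; s = 0.12; √0.88 = 0.938. Size = 2[1 − Φ(2.389)] = 0.017. Gain = 1/0.88 − 1 = 14%. Power is Φ(0.897) = 0.815 without and Φ(1.045) = 0.852 with the terms.

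| ICC | c | Size at R² 0 / 0.1 / 0.3 | Gain at R² 0 / 0.1 / 0.3 | Power at R² 0.3, without / with |
|---|---|---|---|---|
| 0.01 | 0.057 | 0.025 / 0.025 / 0.024 | 0 / 1% / 2% | 0.802 / 0.807 |
| 0.05 | 0.24 | 0.025 / 0.023 / 0.020 | 0 / 2% / 8% | 0.809 / 0.831 |
| 0.10 | 0.40 | 0.025 / 0.022 / 0.017 | 0 / 4% / 14% | 0.815 / 0.852 |

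At ICC 0.1, the detectable d falls from 0.398 to 0.390 (R² 0.1) or 0.373 (R² 0.3).

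**Check by simulation of center means** (20,000 runs, 45 high and 45 low centers, R² 0.3). At ICC 0.1, type I error is 0.017 without the stratum term and 0.025 with it, and power at d = 0.40 is 0.803 and 0.845. At ICC 0.05, type I error is 0.020 and 0.026, and power 0.875 and 0.893.

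**Which term is needed.** A two-wave simulation at ICC 0.1, with the stratum predicting change (R² 0.3), gave rejection rates under the null of 0.019 with no stratum term, 0.025 with a main effect only and 0.034 with stratum by time. That simulation used normal critical values, which are slightly liberal with 90 centers, so the ordering is informative and the levels are not. A main effect alone recovers only part of the loss.

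**The case against.** The strongest reply is that this is a condensed article. Its fixed effects are introduced with *include*, not *only*, and an unseen analysis plan may add stratification terms. That has some force. But the article sets out the fixed effects, random effects, link, test and alpha for this comparison, and names covariates where it intends them, in the client sensitivity analyses. The point therefore concerns the model as stated.

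Second, the harm is conditional. The stratifier is a director's forecast of headcount, with ties at the median split at random, and headcount is not skill acquisition. This stands: at R² = 0 nothing is lost, and no section shows that either factor predicts change.

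Third, ICC 0.1 is the plan's upper bound, and the formula describes a normal test on center means rather than the planned robust score test. Both stand. The lower ICCs are therefore shown, and the sizes are approximations.

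A reader might infer more than the document supports. One could read the mismatch as making the primary test invalid or raising the false-positive rate; the direction is the opposite, and the treatment estimate stays unbiased. One could also read the allocation as three strata (high, low, effectiveness). The median is defined across all 90 centers, and the text does not say whether the 15 were also split high and low, so that structure is not established.

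**Conclusion.** The stated Aim 1 model leaves out both restrictions on the randomization. This can cost efficiency but does not threaten validity. The loss runs from nothing, if the factors do not predict change, to about 4 power points at ICC 0.1 with 30% of between-center variance explained; in that case the nominal 0.025 test runs at about 0.017. At lower ICCs the loss is smaller and at 0.01 it is negligible. These figures rest on an assumed R² of 0–0.3, six providers in every center, no loss to follow-up, a two-sided test, the stated ICC applying to the 8-month change, and a normal approximation. The change is worth making because it is free and the factors are fixed before allocation, not because the planned comparison would mislead.

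**What to change.** In the Aim 1 primary and secondary models, including the 12- and 24-month re-runs, add as fixed effects the randomization factors as they were actually used, each with its interaction with time. These are the participation stratum and effectiveness-center status, or a single combined stratum if the 15 effectiveness centers were not split high and low. State which of the two allocation structures applied. Use the stratum as allocated, not participation as later observed.

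The effectiveness-center term is needed only in the 90-center provider analysis, because all 15 client-outcome centers come from the one separate randomization.

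The cost is a sentence or two of analysis wording and one or two extra terms per wave, affordable with 90 centers. The data are already held, and sample size and conduct do not change. Settling it before outcome data are seen also removes a later choice between adjusted and unadjusted results.
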